#### Statistical Analysis

Baseline characteristics will be summarized overall and stratified by cohort. Continuous variables will be presented as means and SDs or, in the case of skewed distributions, as medians and IQRs. Categorical variables will be reported as absolute counts and corresponding percentages. Comparisons between cohorts will be performed using appropriate statistical tests, including the *t* test (2-sided) or Wilcoxon rank-sum test for continuous variables and the chi-square test or Fisher exact test for categorical variables, as applicable. These analyses are intended to identify potential baseline imbalances between cohorts.

The primary objective is to assess whether implementation of the consensus-validated recommendations is associated with a lower rate of deviations from the recommendations regarding drug selection and dose adjustment. The primary comparison of deviations as defined in the Primary and Secondary End Points section between cohort A (before implementation) and cohort B (after implementation) will be performed using a chi-square test for the dichotomized end point; effect estimates will be reported as odds ratios with corresponding 95% CIs. Additionally, the raw number of deviations (counted as MRPs at the patient level) will be compared between the 2 cohorts using a nonparametric Wilcoxon rank-sum test. If substantial baseline differences between the cohorts are observed, adjusted analyses may be performed using regression models (eg, logistic regression for the binary outcome or Poisson or negative binomial regression for count data) including relevant baseline covariates to account for potential confounding. The main analysis will be conducted at the patient level. In a secondary analysis, the evaluation will be repeated at the prescription level; clustered data structures (multiple prescriptions per patient) will be accounted for using appropriate methods. As the primary objective is to compare prescribing behavior between 2 predefined cohorts within a real-world pretest-posttest design, the primary analysis will be conducted unadjusted for other covariates. To address potential bias, baseline characteristics will be described and compared between cohorts to assess potential imbalances. Furthermore, major organizational changes or parallel quality improvement initiatives related to medication safety will be documented and qualitatively considered when interpreting the results. An exploratory sensitivity analysis using logistic regression adjusting for key clinical variables (eg, age, sex, and Child-Pugh class) will be performed to assess robustness with regard to potential residual confounding. Secondary end points will be analyzed descriptively and, where appropriate, using inferential methods suited to the scale and distribution of the corresponding variables. If distributional assumptions for parametric testing are not met, appropriate nonparametric alternatives will be applied. Missing data will be handled via complete-case analysis without imputation; the extent and pattern of missingness will be described. No formal adjustment for multiple testing will be applied for secondary outcomes, and results will be interpreted accordingly. Analyses will be performed using R (version 4.4.2; R Foundation for Statistical Computing [19]) with RStudio (Posit PBC) [20]. Statistical significance will be set at a *P* value below .05.

### Ethical Considerations

This study is registered in the German Clinical Trials Register, a World Health Organization–recognized primary clinical trial registry under the code DRKS00033779. The protocol was approved by the Ethics Commission of the University of Bonn (2024-464-BO). As the study involves no intervention beyond routine clinical practice and only analyzes routine data from the clinical information system, patient consent is not required for participation in the study. The results will be disseminated at conference meetings and published in peer-reviewed journals.

## Results

The study was supported by funding received in January 2020 (POLAR_MI) and November 2022 (INTERPOLAR-1). The clinical validation phase of this study commenced in January 2025. As of May 2026, 121 patients have been enrolled. Statistical analyses will be conducted in accordance with the predefined analysis plan. Findings from the literature review, the Delphi consensus process, and the clinical validation phase will be reported in subsequent publications. Results of the clinical validation phase are anticipated in late August 2026.

## Discussion

During this study, we will compile evidence-based recommendations on drug selection and dose adjustments for patients with liver cirrhosis; harmonize differing dose recommendations through a Delphi consensus procedure; and apply the recommendations in hospitalized patients with liver cirrhosis in a prospective, pharmacist-led clinical intervention to analyze whether these recommendations will actually be used and contribute to patient safety. These recommendations are intended to support physicians in prescribing appropriate drugs with appropriate doses to patients with cirrhosis in clinical practice. Given the limited and sometimes heterogeneous data available for the use of drugs in liver cirrhosis, the resulting recommendations combine systematically synthesized evidence with structured expert consensus. In the absence of high-level clinical evidence (eg, randomized controlled trials), a structured Delphi consensus provides a formalized and transparent method for generating recommendations within established guideline development frameworks (eg, S2k guidelines according to Association of the Scientific Medical Societies standards) [21]. In contrast to existing drug-specific safety classifications and databases [7], this study will be the first to integrate a systematic literature search with a quality assessment to ensure the inclusion of high-quality evidence, an expert consensus process using the Delphi method, and clinical evaluation of the real-world application of the dose recommendations in hospitalized patients with cirrhosis. This clinical validation on the ward represents a key aspect of our study and differs from similar approaches such as those from Weersink et al [7,22], who developed an expert consensus–based safety classification with dose recommendations for common drugs in patients with cirrhosis. In contrast to Weersink et al [22], who directly integrated their recommendations into a clinical decision support system, our approach will follow a pharmacist-led intervention model. We will provide the developed recommendations to pharmacists working on hepatologic wards. Such investigations of pharmacist-led interventions in hospitalized patients are mainly conducted in geriatric [23-26] and, to a lesser degree, neonatal [27] and pediatric [28,29] patients. However, no such intervention has been conducted specifically in patients with cirrhosis so far. As in similar studies, we will analyze MRPs such as patient adherence [30] and occurrence of ADRs [31] using the dose recommendations identified during the first part of our study.

As an additional unique feature of our approach, the second Delphi round represents a structured re-evaluation under enriched information conditions rather than a purely iterative consensus process. In this context, we plan to specifically provide information about the hepatotoxic effects of the drugs to the experts during the consensus process whenever such data are available [32]. Although Zimmerman [33] reported in 1978 that patients with cirrhosis do not experience drug-induced hepatotoxic effects more frequently than other patients, such events are associated with higher morbidity and mortality due to the preexisting vulnerability. Although only a few publications consider hepatotoxicity in their dose recommendations, we want to analyze whether this information from the literature and the SmPC affects expert decisions regarding dose adjustments. Our modified design of the 2-round consensus procedure allows for the analysis of how clinicians actually manage drug dosing in patients with cirrhosis in the absence of formal guidance and the comparison of how the provision of structured evidence influences expert decisions—a dimension not captured through the conventional approach.

One limitation of our study is the evaluation of a restricted number of drugs. However, we will focus on the drugs with the highest expected clinical relevance for the treatment of patients with liver cirrhosis, determined via reconciliation with the stock list of a hospital of maximum care covering all clinically common drugs and the assessment of relevance based on frequency of use, and on the need for dose adjustments in patients with cirrhosis, determined via an internal consensus procedure. In the future, this initial evaluation could be expanded to additional active substances following the same methodology. The weighting of assessment criteria and the predefined cutoff value for inclusion represent pragmatic thresholds defined to operationalize this prioritization strategy. These parameters are not based on statistical calculations and may limit external validity. As prescribing patterns, formularies, and patient populations may vary across institutions, the prioritization strategy applied in this study may reflect local clinical practice and, therefore, may require contextual adaptation when transferred to other health care settings.

In addition, the Child-Pugh classification [15,16] was used as the primary framework for drug selection and dose adjustment for this study. While the Child-Pugh classification reflects routine clinical practice and forms the basis of most available dosing guidance, it can only serve as a surrogate for hepatic drug metabolism and does not capture other relevant determinants of pharmacokinetics such as renal dysfunction, systemic inflammation, sarcopenia, or portosystemic shunting. Furthermore, the Delphi process is based on the simplified general model of an average hospitalized patient with cirrhosis, excluding atypical or non–cirrhosis-related comorbidities that may independently influence dosing decisions. Accordingly, the resulting recommendations should be interpreted as a basic framework requiring individualized clinical judgment in this heterogeneous patient population. A further limitation concerns the design of the clinical validation phase, which aims to analyze the feasibility and acceptability of the dose recommendations in clinical practice. The pretest-posttest, nonrandomized evaluation reflects real-world constraints but does not allow for causal inference regarding the effectiveness of the recommendations. Observed changes in prescribing behavior may be influenced by temporal effects, increased awareness, or concurrent changes in clinical practice. However, efforts will be made to mitigate these effects by maintaining a stable clinical setting across both study periods (before and after implementation of the recommendations), with consistent senior and ward physicians, and by prospectively capturing physician responses to pharmacist interventions. Both cohorts will be assessed consecutively without temporal gaps and cover comparable time frames, reducing the likelihood of structural changes in care processes or systematic differences in patient management. A prior literature review did not indicate relevant seasonal variation in disease severity of liver cirrhosis that would be expected to systematically bias the comparison. In addition, the primary end point focuses on deviations from recommendations as a process measure rather than clinical outcomes. Further clinical studies with different designs, alternative end points, and larger patient cohorts will be needed to investigate clinical outcomes on a broader scale.

In conclusion, this protocol describes a structured method to establish clinical guidance by compiling and standardizing dose recommendations for patients with liver cirrhosis followed by clinical validation. This approach has the potential to enhance the safety of patients with cirrhosis and contribute to better clinical outcomes.

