**Methods:**

Three steps are planned to establish dose recommendations for patients with liver cirrhosis. First, a systematic literature search will be conducted to identify specific recommendations for drug selection and dosing in cirrhosis, and the literature will be assessed for reporting quality and evidence level. Subsequently, the resulting recommendations will undergo an internal preassessment procedure for relevance of the covered drugs with regard to availability, the clinical impact of adverse drug reactions, the frequency of use, and the expected benefit of dose adjustment. Second, a modified Delphi procedure will be conducted to (1) analyze the clinical handling of the identified drugs by experts in clinical practice in a first round and (2) parse changes resulting from the inclusion of medication-related information and further harmonize differing dose recommendations in a second round. Finally, the adopted dose recommendations will be implemented in a clinical study involving patients with liver cirrhosis to analyze the impact of the recommendations on patient safety.

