#### Delphi Survey on the Dose Recommendations

The Delphi technique is a well-established method for the evaluation and assessment of controversial issues by experts, with the aim to produce reasonably reliable consensus-validated statements [14,17]. A Delphi procedure will be conducted that meets the three basic characteristics: (1) anonymity (the 2-round consensus process will be conducted anonymously; the list of participants will only be disclosed to the experts after the evaluation has been completed), (2) iteration (2 interlinked sequential rounds will be carried out), and (3) controlled feedback (in the second round, participants will receive both the consensus results from the first round and their own initial responses, allowing them to reconsider and, if necessary, adjust their assessments; in this way, convergence of evaluations from the first to the second round can be achieved). Unlike the classic Delphi approach, additional information will be provided to the experts in the second round, which they can incorporate into their assessments. This approach allows experts to reconcile their initial clinical judgments with available evidence and formal guidance.

A total of 12 experts with particular expertise in drug safety in hospitalized patients with cirrhosis and involved in drug decision-making processes in hospitals were recruited: 6 (50%) hepatologists, 3 (25%) clinical pharmacologists, and 3 (25%) clinical pharmacists. The assessment sheets will undergo pretesting in 2 rounds by a pharmacist, a clinical pharmacologist, and 2 hepatologists to identify any issues related to understanding and processing of the sheet, resulting in the final version.

According to the rules of the Association of the Scientific Medical Societies for structured consensus in Germany, a recommendation will be considered accepted if at least 75% of the voting experts agree; Table 1 provides a concise overview of the agreement thresholds and decision categories applied. In contrast, divergence will be assumed if (1) no majority consensus is reached, (2) a majority is achieved but at least one-third of the votes indicate a conflicting recommendation (eg, standard dose vs avoidance), and (3) the majority rejects the evidence but no consensus on an alternative approach can be reached (this item only applies to the second round).

**Table 1. T1:** Grade of consensus.

Grade of consensus	Acceptance (%)	Experts (N=12), n
Strong consensus	≥96	12
Consensus	76‐95	10‐11

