#### First Round of the Delphi Survey: Usual Prescription of the Drugs

The first round is intended to capture the usual prescribing practice concerning the choice of an appropriate active substance (drug selection) within a therapeutic class and dose adjustment of a selected drug. In this design, structured external evidence is not provided in the first round to capture routine expert prescribing behavior prior to evidence-informed reassessment in the second round. In this context, the experts will be asked about their common practice with the active substances in an average hospitalized patient with liver cirrhosis who does not have additional comorbidities that are not typically found in patients with cirrhosis. The experts will have the options to select, for each grade of the Child-Pugh classification, whether they usually (1) prescribe the unchanged dose as they do to patients without liver disease (no dose adjustment), (2) make a dose adjustment, or (3) avoid the drug completely. If they select a dose adjustment, the experts will be required to provide the type of dose adjustment (eg, dose reduction, prolongation of the dosing interval, or dose adaptation based on the results of therapeutic drug monitoring [TDM]). A comment field will be provided for each active substance, allowing experts to describe any limitations and specific considerations that appear relevant to them (for the standardized response options used to capture routine prescribing practice, see Multimedia Appendix 1). This assessment yields a valid and unbiased baseline, is itself an objective of the study, and will provide clinically meaningful data on existing prescribing behavior.

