#### Second Round of the Delphi Survey: Selection of the Dose Recommendations From the Literature

After analysis of the first round, the experts will be asked to review the specific dose recommendations from the systematic literature search and select the recommendations they agree with. Additionally, they will be provided with (1) the authors’ justifications for their recommendations; (2) data from the LiverTox database; and (3) information from the corresponding SmPC on precautions, hepatotoxicity, and ADRs. If the experts completely reject the evidence, they will have the opportunity to enter their own alternative suggestions in a designated comment field. The second round is intended to allow for the analysis of differences between baseline routine clinical judgment and a subsequent evidence-informed reassessment in which experts can critically evaluate and either adopt or explicitly reject the published recommendations. Items for which first-round ratings diverge widely are of particular interest in this round as the provision of structured evidence may facilitate convergence. The design also enables meaningful analysis of substances where first-round consensus was already high to assess whether evidence confirms or challenges prevailing practice.

Of note, the provided data have the same content and structure as in the internal preassessment. For certain agents, the literature provides additional information, such as considerations for comorbidities, specific situations requiring further dose modifications, starting doses, maximum doses, or alternative agents appropriate in cirrhosis. Experts will be asked to provide a separate assessment on their agreement or disagreement for each Child-Pugh grade. The planned evaluation scales can be found in MultimediaAppendices 2  3, which provide the structured assessment forms applied in the second Delphi round. The final recommendation list will include dose recommendations for which consensus is reached.

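### Round 2 of the Delphi gives all experts group feedback and evidence together, so the overall change from round 1 cannot be attributed to the evidence alone, as the Abstract and Discussion state

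*Protocol article*

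**What the plan says.** **Round 1.** According to the section on the first Delphi round, "structured external evidence is not provided in the first round to capture routine expert prescribing behavior". For each Child-Pugh grade the experts state whether they usually "prescribe the unchanged dose as they do to patients without liver disease (no dose adjustment), (2) make a dose adjustment, or (3) avoid the drug" altogether. If they adjust, they also give the type of adjustment, and there is a comment field.

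**Round 2, feedback.** The section Delphi Survey on the Dose Recommendations says that "in the second round, participants will receive both the consensus results from the first round and their own initial responses", and gives the purpose: "in this way, convergence of evaluations from the first to the second round can be achieved".

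**Round 2, evidence.** The same section says that "additional information will be provided to the experts in the second round, which they can incorporate into their assessments". The section on the second round lists the content: published recommendations with their authors' justifications, LiverTox data and SmPC text. The task is now to "review the specific dose recommendations from the systematic literature search and select the recommendations they agree with", with agreement or disagreement given for each Child-Pugh grade.

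**The claim.** The Abstract (Methods) says the second round will "parse changes resulting from the inclusion of medication-related information". The Discussion says the design allows "the comparison of how the provision of structured evidence influences expert decisions" and presents this as something a conventional Delphi does not capture. It adds the aim of finding out whether hepatotoxicity information affects dosing decisions.

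**The caveat.** The limitations paragraph of the Discussion disclaims causal inference for the clinical before-after phase. It makes no such statement for the Delphi.

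**The concern.** The Delphi is itself an uncontrolled before-after comparison on a single panel. Between the two measurements every expert receives at least two inputs that can move an answer: sight of the group result and of their own earlier answer, and the evidence package. The plan expects convergence from the first (general Delphi section) and says the second may also bring it about (second-round section). It then words the aim in the Abstract and Discussion as if the second were responsible.

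At stake is a stated analytic aim and a novelty claim. If the Delphi results are reported in the terms of the Abstract, ordinary convergence on a majority could be described as experts being persuaded by evidence, or by hepatotoxicity data in particular.

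**Working it through.** There is no figure in the plan to reproduce. The check is a comparison of conditions, an identifiability check and an illustration of size.

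**1. Conditions side by side**

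| | Round 1 | Round 2 |
|---|---|---|
| Group result and own earlier answers | none | all 12 experts |
| Evidence package | none | all 12 experts |
| Task | report usual practice per Child-Pugh grade | select, agree or disagree with published recommendations per Child-Pugh grade |

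No step lies between the rounds, and no second panel receives only one of the inputs.

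**2. What the overall change can identify**

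Write each expert's answer as baseline + F·(feedback) + E·(evidence) + T·(task).

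- Round 1 row: (1, 0, 0, 0).
- Round 2 row: (1, 1, 1, 1).
- Stacked for 12 experts, the matrix has rank 2 for 4 parameters.

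Only the baseline and the sum F + E + T can be estimated. More experts or more drugs do not change this for the overall change. If the two tasks are taken as equivalent (T = 0), F and E still cannot be separated.

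**3. Hepatotoxicity information**

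E is itself a sum over recommendations, justifications, LiverTox data and SmPC text. For each drug all experts see the same package at once, so the part due to hepatotoxicity information is not identified even if F were zero.

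**4. Illustration of size**

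Inputs from the plan: 12 experts, so one vote is 1/12 = 8.3 percentage points; acceptance at 75% or more is 9 of 12. Assumptions (not in the plan): the evidence effect is zero, no majority expert leaves, and each minority expert joins the majority on feedback alone, independently, with probability c between 0.1 and 0.5.

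With m experts in the majority in round 1 and k = 12 − m outside it:

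- Expected agreement = (m + k·c)/12.
- P(at least 9) = P(Binomial(k, c) ≥ 9 − m).

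For m = 7 (58%), k = 5:
- c = 0.1: agreement 7.5/12 = 63%; P = 1 − 0.9⁵ − 5·0.1·0.9⁴ = 0.08.
- c = 0.5: agreement 9.5/12 = 79%; P = 1 − 6/32 = 0.81.

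For m = 8 (67%), k = 4:
- c = 0.1: agreement 8.4/12 = 70%; P = 1 − 0.9⁴ = 0.34.
- c = 0.5: agreement 10/12 = 83%; P = 1 − 0.5⁴ = 0.94.

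Table 1 uses the label of consensus from 10 of 12 upwards. For that line the corresponding probabilities are 0.01 to 0.50 (from 7) and 0.05 to 0.69 (from 8).

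**5. Item-level information that remains**

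- Literature agrees with the round 1 majority: feedback and evidence push the same way, so movement towards the majority is uninformative about evidence.
- Literature conflicts with the round 1 majority: conformity pushes towards the majority and evidence away from it. Net movement away from the majority is not explained by conformity, although the changed task may still contribute.

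**The case against.** Several points on the other side have force.

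- **The second-round section is largely descriptive.** It speaks of analysing differences between baseline judgement and an evidence-informed reassessment, and says only that evidence may help convergence. This stands. The overreach is in the Abstract and the Discussion, and the second-round section is the model for correcting them.
- **Feedback is not a constant input.** Its direction differs by drug and Child-Pugh grade, and the plan intends to examine items with high first-round consensus to see whether the evidence confirms or challenges practice. This stands too. The rank check codes feedback as present or absent and so applies to the overall change only. A reader might infer that nothing can be learned about evidence, or that its share could be anything from none to all for every item. The documents do not support that, because movement away from a majority is not conformity.
- **The change of task may be minor.** Both rounds are answered per Child-Pugh grade, and the extracted recommendations (adjustment, interval change, avoidance, no adjustment) may map onto the round 1 options. No mapping is stated, and the forms are in appendices that are not shown. The task is therefore only a possible contributor.
- **Feedback is a defining Delphi feature, included deliberately.** True, and it should stay. Its inclusion is the reason the attribution has to be limited.

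A reader might also infer that every rise in agreement will be reported as an effect of evidence. The plan does not say so; it credits feedback with convergence in its general Delphi section.

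**Conclusion.** The point holds as a limit on inference. The overall change from round 1 to round 2 cannot be attributed to the evidence, as the Abstract and Discussion word it, and an effect of hepatotoxicity information cannot be isolated. For the overall change and for hepatotoxicity this follows from how the data are collected, so an analysis plan could not repair it. The total change, and the adoption or rejection of published recommendations, can still be described.

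The amount by which feedback could mimic an evidence effect is not known. The 0.08 to 0.81 range for an item starting at 7 of 12 rests entirely on the assumed switching rates and shows only that the effect need not be trivial.

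It would be wrong to infer that the recommendation list or the clinical comparison is undermined. Acceptance depends on the level of agreement reached, whatever produced it, and the clinical primary end point does not use the change between rounds. The matter concerns a secondary analytic aim and a novelty claim. It is worth correcting because the Delphi findings are still to be published.

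**What to change.** 1. **Reword the claim** in the Abstract (Methods) and in the Discussion, in line with the descriptive aim of the second-round section. For example: *changes between rounds reflect evidence and group feedback combined, and possibly the changed task; they are not attributed to the evidence, or to hepatotoxicity information, alone.*
2. **Extend the causal caveat** in the limitations paragraph from the clinical phase to the Delphi.
3. **Report changes separately** for items where the literature agrees with the round 1 majority and items where it conflicts, per Child-Pugh grade. State how published recommendations are mapped to the round 1 categories, and list items without a round 1 majority apart.
4. **Only if round 2 has not been run:** before any group result is shown, collect an evidence-informed answer on intended management in the round 1 categories. Asking about intended management matters, because usual practice does not change on reading a form. This would still not isolate hepatotoxicity information.

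Step 4 is probably too late. The clinical phase began in January 2025 and comprises two consecutive 9-month cohorts. If that schedule held, the cohort using the recommendations began around October 2025 (January 2025 plus 9 months), after round 2. This is an inference, since the article describes the Delphi in the future tense.

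Steps 1 to 3 cost a few sentences, one stratified table and a less favourable novelty claim. Step 4 would cost three extra answers per substance, one for each Child-Pugh grade.
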